**Methods:**

VitCAP is a single-center, double-blind, placebo-controlled, parallel-group randomized clinical trial conducted at a tertiary hospital in Australia. Adults aged 18 years and older hospitalized with CAP will be randomized within 48 hours of admission in a 1:1 ratio to receive either oral sodium ascorbate (1 g 3 times daily for 7 days, followed by 500 mg twice daily for 30 days) or a matching placebo in addition to standard care. Randomization will be computer generated with allocation concealment via a centralized pharmacy service, and all participants, clinicians, investigators, and outcome assessors will remain blinded. The primary outcome is time to clinical stabilization, defined using standard physiological criteria. Secondary outcomes include early clinical response, symptom burden at 30 days, intensive care unit admission, need for ventilatory or vasopressor support, LOS, all-cause mortality at 30 days and 6 months, hospital readmission, health-related quality of life, and changes in inflammatory biomarkers (C-reactive protein and procalcitonin). Analyses will follow the intention-to-treat principle. The primary outcome will be analyzed using Cox proportional hazard regression adjusted for prespecified covariates, with sensitivity analyses including restricted mean survival time.

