### Study Aim and Hypotheses

The primary aim of the VitCAP trial is to determine whether high-dose oral vitamin C (sodium ascorbate) administered during hospitalization and continued for 30 days after discharge improves clinical recovery in adults hospitalized with CAP when compared with placebo alongside standard care. The primary hypothesis is that vitamin C supplementation will reduce the time to clinical stabilization compared with placebo.

Secondary hypotheses are that vitamin C supplementation will (1) improve early clinical response; (2) reduce hospital LOS; (3) decrease the need for intensive care, ventilatory support, or vasopressors; (4) reduce mortality and hospital readmission; (5) improve patient-reported symptom burden and HRQOL; and (6) reduce systemic inflammatory biomarkers, including C-reactive protein and procalcitonin.

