### Outcomes

The primary outcome is *time to clinical stabilization*, defined as the time from randomization to meeting all the criteria.

The primary and secondary outcomes have been provided in Textbox 2.

Primary and secondary outcomes.

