**Secondary outcomes**
Early clinical response [22], defined as improvement in at least 2 of 4 specific symptoms (chest pain, cough, sputum production, and dyspnea) without any symptom worsening 3 to 5 days after randomizationImprovement in community-acquired pneumonia–related symptoms at 30 days from the day of randomization, measured using the 18-item community-acquired pneumonia symptom questionnaire [23] (range 0-90)Intensive care unit admissionRequirement for noninvasive or invasive mechanical ventilationVasopressor useLength of hospital stayAll-cause mortality at 30 days and 6 months30-day hospital readmissionHealth-related quality of life at 1 and 6 months using the EQ-5D-5L [24]Inflammatory biomarkers (C-reactive protein and procalcitonin) measured at baseline and day 7 or discharge

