#### Secondary Outcome Analysis

Hospital LOS will be analyzed similarly using *t* tests or linear regression, with Cox regression as a secondary analysis. Although LOS data are likely to be nonnormally distributed, the *t* test and linear regression models are considered robust due to the sample size (n>30 per group), which satisfies the conditions of the central limit theorem.

HRQOL at 1 and 6 months will be assessed using linear mixed-effects models to account for repeated measures, and binary outcomes (eg, ICU admission and in-hospital mortality) will be compared using logistic regression. Biomarkers will be analyzed as change from baseline with adjustment for time from randomization to follow-up sampling. Linear regression and mixed-effects models incorporating time as a covariate will be used, with sensitivity analyses restricted to samples collected within a predefined time window.

Baseline differences between groups in clinical and demographic variables will be assessed using *t* tests, Wilcoxon rank-sum tests, or chi-square or Fisher exact tests as appropriate. Missing data will be addressed using multiple imputation, and additional sensitivity analyses will be performed in subgroups, such as patients with moderate to severe pneumonia (CURB-65 score≥2).

Statistical significance for all outcomes will be determined using a 2-sided type I error rate of α=.05. All analyses will be performed using Stata (version 19.0; StataCorp).

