#### Subgroup Analyses

Prespecified subgroup analyses will examine the effects of vitamin C in clinically important subgroups, including older participants (aged <65 years vs ≥65 years), participants with frailty (Clinical Frailty Scale score of 1-5 vs ≥5), participants with moderate to severe pneumonia (CURB-65 score of <2 vs ≥2), and participants with higher multimorbidity burden (Charlson Comorbidity Index of <3 vs ≥3). Separate regression models will be performed for each subgroup.

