### Comparison With Prior Work

Previous interventional studies [14,16,17] evaluating vitamin C in pneumonia and sepsis have yielded heterogeneous results, largely due to differences in patient populations, dosing regimens, formulations, and abrupt therapy cessation. Most trials have focused on patients with sepsis who are critically ill, often using intravenous ascorbic acid and short treatment durations, and have not prioritized patient-centered outcomes such as symptom burden, recovery trajectory, or HRQOL. The VitCAP trial seeks to address these gaps by evaluating oral sodium ascorbate administered over an extended period in a broader population of hospitalized patients with CAP.

The primary outcome of time to clinical stabilization is clinically meaningful, reproducible, and closely linked to patient recovery and health care use. Secondary outcomes capture early response, longer-term symptoms, readmissions, and quality of life, thereby providing a comprehensive assessment of both short- and medium-term benefits. The inclusion of inflammatory biomarkers will also allow for the exploration of potential mechanistic pathways and identification of patient subgroups most likely to benefit from supplementation.

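### One two-sided .05 significance rule covers all ten secondary items (up to 13 comparisons), with no hierarchy, no gate on the primary and no general exploratory label

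*Protocol article*

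**What the plan says.** The protocol article names one primary outcome. Under Outcomes: "The primary outcome is *time to clinical stabilization*, defined as the time from randomization to meeting all the criteria". The sample size rests on that outcome alone, at two-sided .05.

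Under Secondary Outcome Analysis, the significance rule is general: "Statistical significance for all outcomes will be determined using a 2-sided type I error rate of α=.05".

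Under Study Aim and Hypotheses, the secondaries are framed as directional: "Secondary hypotheses are that vitamin C supplementation will (1) improve early clinical response; (2) reduce hospital LOS; (3) decrease the need for intensive care", and the list continues with ventilatory or vasopressor support, mortality and readmission, symptoms and quality of life, and biomarkers. Two items in Textbox 2 have two time points each: mortality (in the Abstract's wording, "all-cause mortality at 30 days and 6 months") and the EQ-5D-5L. The biomarker item covers two markers.

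Under Comparison With Prior Work, the secondaries are described as "thereby providing a comprehensive assessment of both short- and medium-term benefits". The closest thing to an exploratory label is in the same section and concerns the biomarkers only.

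Under Subgroup Analyses: "Separate regression models will be performed for each subgroup". There are four factors with two levels each. That section gives no significance level of its own.

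**The concern.** The rule is stated, not left open. It gives every secondary comparison the full two-sided .05, and nothing elsewhere in the article ranks the secondaries, makes them depend on the primary or says they are not for claims. With many comparisons in 124 patients, a nominally significant secondary is quite likely to appear by chance even if vitamin C does nothing. The published rule would then let it be called statistically significant beside a null primary. The article's Conclusions expect the results to inform practice and guidelines. Its limitations section concedes low power for mortality but does not limit how a nominally significant secondary may be reported.

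**Working it through.** **The plan's own figure.** The article gives no family-wise error rate. Its use of .05 for the primary reproduces. With a difference of 1.1 days, SD 1.95, 80% power and two-sided .05, n per group = 2 × (1.96 + 0.84)² × (1.95/1.1)² ≈ 49.3, so 50. The t-based version gives 50.3, so 51 per group and 102 in total, as stated. The whole .05 is spent on the primary.

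**Counting the secondaries (Textbox 2).**

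| Item | Comparisons |
|---|---|
| Early clinical response | 1 |
| Symptom score at 30 days | 1 |
| ICU admission | 1 |
| Ventilation | 1 |
| Vasopressors | 1 |
| Length of stay | 1 |
| Mortality (30 days, 6 months) | 2 |
| Readmission | 1 |
| EQ-5D-5L (1 and 6 months) | 2 |
| CRP and procalcitonin | 2 |
| **Total** | **10 items, 13 comparisons** |

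The count is not fixed by the text. The mixed model for quality of life may give one treatment test instead of two, which makes 12. Secondary Outcome Analysis also names in-hospital mortality, which Textbox 2 does not list and which would make 14.

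**Chance of at least one false positive, all nulls true, each test of size .05.** For independent tests this is 1 − 0.95^k. For correlated tests, the statistics are taken as normal with a common correlation ρ and a critical value of 1.96, by numerical integration. The documents give no correlation, so ρ is an assumption and a range is shown.

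| k | ρ = 0 | ρ = 0.5 | ρ = 0.8 |
|---|---|---|---|
| 10 | 40% | 29% | 17% |
| 13 | 49% | 33% | 19% |
| 14 | 51% | 35% | 20% |

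For 13 tests that is 0.192/0.05 = 3.8 to 0.487/0.05 = 9.7 times .05. Counting only errors that favour vitamin C, 13 independent tests give 1 − 0.975^13 = 28%.

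**How far the nominal size holds.** Seven of the 13 comparisons are binary: early response, ICU, ventilation, vasopressors, two mortality times and readmission. They are to be analysed by logistic regression. The exact null size of the unadjusted Wald test at 62 per arm is:

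| Event rate (both arms) | Actual size |
|---|---|
| 5% | 0.005 |
| 8% | 0.021 |
| 10% | 0.031 |
| 17% | 0.046 |

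The event rates are assumptions, except that 17% is close to the 16.9% 30-day mortality quoted in the Background. The effect on the 13-test figure, under independence:

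- Three binary outcomes at a 5% event rate: 1 − 0.95^10 × 0.995^3 = 41%.
- All seven at 5%, an extreme case: 1 − 0.95^6 × 0.995^7 = 29%.

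The nominal expected count, 13 × 0.05 = 0.65 false positives, falls in the same way.

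**The case against.** The strongest reply is that this is convention and condensation. A trial with one primary outcome commonly reports secondaries at a nominal .05. A hierarchy or an interpretive label may well sit in an analysis plan that is not shown, and its absence from an article is no fault. The article also separates the primary clearly: one outcome, one primary hypothesis, and a sample size built on it alone. No sentence says that a significant secondary will support an efficacy claim.

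Much of this stands. The primary is protected, and the step from significant secondary to claimed benefit is one that a reader might take; the article does not take it. What remains is that the article is not silent. It sets a rule for every outcome, and an analysis plan that called the secondaries exploratory would leave that published sentence needing qualification.

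Two stronger readings are tempting and are not supported:

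- **Subgroups.** A reader might infer that the models in the eight strata are each judged at .05 and add them to the 13, making 21 tests (66% if independent). The .05 sentence speaks of outcomes, and Subgroup Analyses sets no level and does not say which outcomes are modelled. Any such figure is conditional on applying .05 there too. On that condition, eight strata on one outcome give about 25%, assuming four independent factors each split evenly.
- **A single headline risk.** A reader might take one in three as the result. It holds for 13 tests only at an assumed common correlation of about 0.5.

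**Conclusion.** The point holds in a limited form. As written, the rule lets any of 10 secondary items (up to 13 comparisons) be declared significant at two-sided .05 whatever the primary shows, and the article's directional hypotheses make that reading natural. The nominal chance of at least one false-positive secondary under the global null is 19% to 49% for 13 tests and 17% to 40% for 10. This rests on equal pairwise correlation between 0.8 and 0 and on each test having size .05. It is lower where binary events are rare.

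The documents do not support a claim that the primary's type I error is inflated: there is one primary outcome tested at .05. What is at risk is over-reading of secondary results, so the change is worth making but the severity is modest.

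**What to change.** Restate the significance sentence in Secondary Outcome Analysis along these lines: *The two-sided .05 level for an efficacy claim applies to the primary outcome only. Secondary outcomes and subgroup analyses will be reported as estimates with 95% CIs, without adjustment for multiplicity, and interpreted as supportive or exploratory.* Align Study Aim and Hypotheses by giving the six secondary hypotheses the same status.

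Optional alternative: if claims are wanted on a few secondaries, name them and test them in a fixed order, each at two-sided .05 and only after the primary and every earlier test are significant. All the others stay exploratory.

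The cost is wording. It needs no extra patients or data and does not change the primary test or its power. Recruitment is scheduled for 2026 and analysis follows the end of follow-up, so the change can be made before any unblinded result exists. The downside is that an isolated secondary P<.05 can no longer be reported as an established benefit.

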#### Subgroup Analyses

Prespecified subgroup analyses will examine the effects of vitamin C in clinically important subgroups, including older participants (aged <65 years vs ≥65 years), participants with frailty (Clinical Frailty Scale score of 1-5 vs ≥5), participants with moderate to severe pneumonia (CURB-65 score of <2 vs ≥2), and participants with higher multimorbidity burden (Charlson Comorbidity Index of <3 vs ≥3). Separate regression models will be performed for each subgroup.

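### The frailty subgroups overlap at Clinical Frailty Scale score 5, and the separate subgroup models as stated give no test of whether the treatment effect differs

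*Protocol article*

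**What the plan says.** The Subgroup Analyses section of the protocol article opens with "Prespecified subgroup analyses will examine the effects of vitamin C in clinically important subgroups" and names four factors, each with its split in parentheses:

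- age: "older participants (aged <65 years vs ≥65 years"
- frailty: "participants with frailty (Clinical Frailty Scale score of 1-5 vs ≥5"
- pneumonia severity: "participants with moderate to severe pneumonia (CURB-65 score of <2 vs ≥2"
- multimorbidity: "participants with higher multimorbidity burden (Charlson Comorbidity Index of <3 vs ≥3"

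It then gives its one statement of method: "Separate regression models will be performed for each subgroup". The article nowhere mentions a treatment-by-subgroup interaction term, a test of heterogeneity or a multiplicity rule for the subgroups. The Secondary Outcome Analysis section also lists a restriction to CURB-65 of 2 or more among its sensitivity analyses, and sets the threshold: "Statistical significance for all outcomes will be determined using a 2-sided type I error rate of α=.05".

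**The concern.** There are two separate faults in what the section fixes.

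First, the frailty split does not define two groups. A participant scoring 5 meets both definitions, so run as printed the plan enters that participant in both frailty models, and the two estimates share data. If the slip is noticed only at analysis, someone must place the score-5 participants after the fact, and the split is then no longer prespecified.

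Second, each factor names both sides of a split, which invites the reader to compare them, but models fitted within each stratum do not make that comparison. Each gives an effect and a P value against zero for its own stratum. When one stratum falls below .05 and the other does not, it is easy to read this as benefit in one kind of patient and not in the other. In a trial of this size that pattern is common even when the effect is the same everywhere.

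**Working it through.** **Step 1. The overlap.** For whole-number scores, the first category takes scores from 1 up to 5 and the second takes 5 and above. Scores 1 to 4 meet only the first, scores above 5 only the second, and score 5 meets both. The other three factors all use a strict below-k versus k-or-above form, in which no value can meet both.

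The article gives no distribution of frailty scores. If 10%, 20% or 30% of 102 analysed participants score 5 (assumed), the two frailty models together hold 102 × 1.1 = 112, 102 × 1.2 = 122 or 102 × 1.3 = 133 participant records.

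**Step 2. The plan's own sample size.** Inputs from Sample Size Calculation: difference 1.1 days, SD 1.95, two-sided α .05, power 80%. The normal formula is n per group = 2 × [1.95 × (1.960 + 0.842) / 1.1]² = 49.3, rounded up to 50. The t-distribution version gives 50.3, rounded up to 51 per group, or 102 in total. This reproduces the article's figure, so the same inputs are used below.

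**Step 3. Separate models when the effect is uniform.** Assume the true effect is 1.1 days in both strata. With n per arm in a stratum, SE = 1.95 × √(2/n) and power ≈ Φ(1.1/SE − 1.96). The two strata contain different people, so P(exactly one significant) = p₁(1 − p₂) + p₂(1 − p₁). The article gives no subgroup shares, so splits from 50/50 to 20/80 are assumed. N is taken as 102 (the required number) and as 124 (all recruited, no attrition).

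Example, N = 124 split 50/50: n = 31 per arm in each stratum, SE = 0.495, power = Φ(2.221 − 1.960) = 0.603, discordance = 2 × 0.603 × 0.397 = 0.479. The t-distribution version gives power 0.589 and discordance 2 × 0.589 × 0.411 = 0.484.

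**Step 4. The interaction test.** For the difference between two stratum effects, SE = 1.95 × √(2/n_A + 2/n_B), where n_A and n_B are the per-arm sizes in the two strata. The last column is the power to detect a 1.1-day difference in effect. Example, N = 124 split 50/50: SE = 0.700, 1.1/0.700 = 1.570, power ≈ 0.349.

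| N | Split | Power, smaller / larger stratum | Exactly one significant (uniform effect) | Interaction power (1.1-day difference) |
|---|---|---|---|---|
| 102 | 50/50 | 0.522 / 0.522 | 0.499 | 0.296 |
| 102 | 40/60 | 0.437 / 0.597 | 0.512 | 0.287 |
| 102 | 30/70 | 0.345 / 0.664 | 0.551 | 0.257 |
| 102 | 20/80 | 0.246 / 0.722 | 0.612 | 0.207 |
| 124 | 50/50 | 0.603 / 0.603 | 0.479 | 0.349 |
| 124 | 40/60 | 0.511 / 0.682 | 0.496 | 0.337 |
| 124 | 30/70 | 0.405 / 0.748 | 0.547 | 0.302 |
| 124 | 20/80 | 0.289 / 0.802 | 0.627 | 0.241 |

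With a uniform effect, a significant/non-significant split appears 48% to 63% of the time per factor. An interaction test at .05 would wrongly signal a difference 5% of the time per factor, or 1 − 0.95⁴ = 18.5% over four factors if they were independent. That last figure is why even the interaction results need an exploratory label.

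**The case against.** The frailty overlap looks like a one-character slip. The three clean splits show that two distinct groups were intended, and double counting occurs only if the slip reaches the analysis code. That is fair, but the text does not show which end is wrong: 1-4 versus ≥5 and 1-5 versus >5 each keep one printed category. A programmer cannot settle it, so the sponsor must.

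The sentence on separate models could also mean one model per factor, which might contain an interaction term. That reading is possible. The within-stratum reading is the more natural one, and no interaction is mentioned anywhere, so the sentence needs rewriting either way. A separate analysis plan may add an interaction test. However, the article does not leave the method open: it states one, and on its natural reading that method does not compare strata.

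A reader might infer that effect modification is to be judged by comparing P values across strata, or that the trial intends to declare who benefits. The documents do not support that. The section says only that effects will be examined. The phrase "identification of patient subgroups most likely to benefit from supplementation" in Comparison With Prior Work refers to the inflammatory biomarkers, not to these four factors. A reader might also suppose that every stratum model carries the full covariate list. The article attaches that list to the primary Cox model and the linear sensitivity model, and does not say what the subgroup models include.

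Finally, the percentages are not properties of this trial. They rest on a t-test rather than the Cox model, on assumed splits and, for N = 124, on no attrition. They matter only if discordant significance is interpreted. All of this stands, and the figures are offered as illustration.

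**Conclusion.** Both parts hold as statements about the text. The frailty categories overlap at score 5 and must be made exclusive. The stated subgroup method, read naturally, gives no test of whether the effect differs. The size of the second fault is illustrative: 48% to 63% discordance per factor under a uniform 1.1-day effect, assuming SD 1.95, a two-sample comparison of means, 102 or 124 participants and splits between 50/50 and 20/80.

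This is a should-fix point. The subgroup analyses are secondary, and neither fault touches the primary estimate, its model or the sample size. It would go too far to say that the subgroup plan threatens the trial's main conclusion.

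**What to change.** 1. Make the two frailty categories mutually exclusive, with the sponsor stating which holds score 5 (1-4 versus ≥5, or 1-5 versus >5), before any unblinded look at the data.
2. Replace the separate-models sentence. For each factor, one model will be fitted to all participants with treatment, factor and treatment-by-factor interaction. The interaction estimate will be reported with its 95% CI, and the subgroup effects will be taken from that model and presented as exploratory.

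The cost is two sentences in the protocol or analysis plan and no new data. The downside is low power: on the same illustrative basis, about 21% to 35% for a 1.1-day difference in effect. A non-significant interaction must therefore not be read as evidence that the effect is the same in both strata.

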### Safety Monitoring

#### Adverse Events

An adverse event (AE) is any untoward medical occurrence, including symptoms, signs, illnesses, or abnormal laboratory findings, that develops or worsens during the trial irrespective of causality. All AEs will be recorded from randomization until completion of follow-up.

